## **15. Staff training and awareness**

For paramedics based within stations / teams randomised to deliver the PASTA pathway, study specific training will be provided via a securely hosted online video. This will include explanation of the study objectives, demonstration of the PASTA pathway processes, completion of trial documentation and responses to adverse events. After watching the video, paramedics will complete an online MCQ knowledge assessment. Paramedics who do not provide correct responses to all questions will be invited to watch the online video again and repeat the MCQ. Paramedics who correctly answer all questions will be identified as trained and issued with study documentation. If paramedics based with stations / teams allocated to delivering the intervention do not wish to assist with the study, they will be able to opt out of training.

Paramedics based with stations / teams randomised to continuing standard stroke care will be informed that there is an ongoing study of pre-hospital assessment for stroke patients, but not be given any further information about the study and asked not to change their practice. Paramedics allocated to continuing standard stroke care will also be able to opt out of the study if they wish.

To determine whether the characteristics of paramedics participating in each study group differ, the following will be obtained about individual randomised paramedics during the course of the study: age, gender, highest qualification, years qualified as a paramedic, years in service at employing ambulance service, NHS job band, job title. These characteristics will be obtained from ambulance service records if possible and if not, direct from paramedics by means of an electronic survey.

NHS research support staff based in hospitals taking part in the study will receive study specific training. This will cover identification, recruitment and consent of participants, data collection and the 90 day research assessment, and other study processes such as use of the online database.

Clinical staff at hospitals taking part in the study will be made aware of the trial at service meetings and by email, but will not receive additional protocol-related research training or documentation. Hospital services will not be expected to change their standard local care process for patients undergoing thrombolysis treatment assessment as part of the study. They will continue to provide clinical care for all study patients consistent with the information and prompts provided by all paramedics within the context of the local service setting. If services change their configuration and standard care process during the study as a quality

improvement initiative, this would apply to all stroke admissions and would not prevent the delivery of the paramedic-led PASTA intervention.

## 16. Study withdrawal

No specific withdrawal criteria have been pre-set. Participants may withdraw from the study at any time for any reason. Data collected prior to withdrawal will be used in the study analysis unless the patient or their representative requests that this should not be the case. Should a decision to withdraw from the study be made, a reason for withdrawal will be sought but participants can choose to withdraw without providing an explanation.

Occasionally, further clinical tests and information obtained result in a diagnosis of stroke being revised to an alternative diagnosis at a later date. Such patients will not be withdrawn from the study as initial care processes received were for a diagnosis of stroke.

## 17. Safety evaluation

The standard definitions for adverse events will be used in this study:

**Adverse event (AE):** Any untoward medical occurrence in a subject to whom a study intervention or procedure has been administered, including occurrences which are not necessarily caused by or related to that intervention. An AE, therefore, does not necessarily have a causal relationship with the treatment. In this context, “treatment” includes all interventions (including comparative agents) administered during the course of the study. Medical conditions/diseases present before starting study treatment are only considered adverse events if they worsen after starting study treatment.

**Related AE:** An AE that results from administration of any of the research study procedures. All AEs judged by either the reporting investigator or the sponsor as having reasonable causal relationship to a study procedure qualify as ‘related adverse events’. The expression “reasonable causal relationship” means to convey in general that there is evidence or argument to suggest a causal relationship.

**Causality:** The assignment of the causality should be made by the investigator responsible for the care of the participant. All adverse events judged as having a reasonable suspected causal relationship to a study procedure are considered to be related adverse events. If any doubt about the causality exists, the local investigator (PI) should inform the Chief Investigator. In the case of discrepant views on causality between the investigator and others, all parties will discuss the case. In the event that no agreement is made, the main REC and other bodies will be informed of both points of view.

**Serious Adverse Event (SAE):** an untoward occurrence that:-

- Results in death
- Is life-threatening (refers to an event in which the subject was at risk of death at the time of the event; it does not refer to an event which hypothetically might have caused death if it were more severe)
- Requires inpatient hospitalisation, or prolongation of existing hospitalisation
- Results in persistent or significant disability or incapacity
- Consists of a congenital anomaly or birth defect
- Is otherwise considered medically significant by the investigator

Medical judgement should be exercised in deciding whether an AE is serious in other situations. Important medical events that are not immediately life-threatening or do not result in death or hospitalisation but may jeopardise the patient or may require intervention to

prevent one of the other outcomes listed in the definition above, should also be considered serious.

**Unexpected Adverse Event:** An adverse event that is not an expected occurrence in the circumstances of this trial.

### **Expected adverse events**

The PASTA pathway is embedded into standard clinical practice for a clearly defined time interval, during which patients will be closely supervised by qualified ambulance and hospital professionals. Deterioration in the health status of stroke patients commonly occurs in clinical practice: average inpatient mortality is 17% in NHS services[5]; 2% patients treated with thrombolysis deteriorate due to the recognised side effect of cerebral haemorrhage[6]; the stroke recurrence rate is up to 6% within the first 3 months[27]. The following are therefore expected adverse events:

Death directly due to the initial stroke.  
Thrombolysis related cerebral haemorrhage.  
Stroke recurrence leading to new hospitalisation.

### **Recording and reporting of adverse events**

This study will only report adverse events which are considered to be serious.

In addition, apart from death, adverse events which are considered to be serious will only be reported up until seven days after study entry (ie for one week after the date of the paramedic assessment).

After seven days, there is no possible mechanism by which the study intervention can cause new adverse events. This approach mirrors other clinical trials of emergency stroke treatment where the longer term risk of unforeseen adverse events from the study intervention is very low. Any adverse events that do occur will be in the immediate peri-admission period as the intervention has been designed to facilitate the emergency administration of intravenous thrombolysis to appropriate stroke patients. Thrombolysis treatment is widely used in clinical practice and its adverse events are already well described. It can only be given once within 4.5 hours of stroke onset and has lost all pharmacological action within 24 hours. The study intervention does not change the clinical criteria for thrombolysis administration. Therefore it is not possible for any adverse events after the emergency phase to be attributed to the study intervention. To provide additional reassurance, the reporting period has been set at 7 days rather than just 24 hours.

Deaths will be recorded for the duration of a participants involvement in the study (until 90 days after stroke).

Serious Adverse Events will also **exclude**:

- The expected adverse events listed above (these will be routinely recorded and monitored as part of study data collection)
- Pre-planned hospitalisations and scheduled treatment for pre-existing conditions.

A study SAE form will be completed for all SAEs. To ensure complete capture of SAE's, the 90 day study CRF will include a question to ask staff to check for medical events that fulfil the criteria to be a SAE. For any events which fulfil the above criteria to be a SAE and are unreported, the study SAE form will be completed.

Serious adverse events, regardless of causality or expectedness, will be reported to the Chief Investigator. SAEs will also be reported to the trial sponsor (Newcastle Upon Tyne

Hospitals NHS Foundation Trust) in line with sponsor policies. The initial report can be made by telephone or email to the study co-ordinating centre. All provisional reports must be followed by a fully completed form. If incomplete information is available at the time of this initial report, further information must be provided on a follow up form as soon as it is available. The main REC will be notified of related and unexpected SAEs within 15 days of the Chief Investigator becoming aware of the event.

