### **10.2 Standard stroke care (comparison group)**

Patients in the comparison group will receive standard stroke care as per current local ambulance and hospital clinical protocols, which are reinforced by national clinical guidelines and audit. The study will not provide comparison group paramedics with additional training or documentation to support information collection, clinical communication or processes after hospital arrival.

The local thrombolysis assessment and treatment processes in hospital will not be deliberately altered. It is routine practice that all patients receiving thrombolysis are observed for at least 24 hours and undergo repeat CT brain imaging at 24-48 hours to exclude intracranial haemorrhage. Recognised complications of thrombolysis include allergic reactions (angioedema), extra-cranial haemorrhage and intracranial haemorrhage causing symptomatic neurological deterioration (defined as with an increase in NIHSS  $\geq 4$  points within 36 hrs of thrombolysis associated with parenchymal haemorrhage on repeat brain imaging)[24].

Whether or not they receive thrombolysis, all patients with acute stroke should be admitted to an ASU within 4 hours of hospital arrival in order to receive specialist assessment and care tailored to their individual needs. The overall length of stay in hospital reflects pre-morbid conditions and dependency, stroke severity and subsequent medical complications (e.g. pneumonia, thromboembolism, stroke recurrence), progress during rehabilitation, personal social circumstances and the local availability of services to provide further rehabilitation and care in the community (including generic and stroke-specific early supported discharge teams and community rehabilitation teams).

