#### Day 2 thrombolysis outcome (if administered):

Stroke severity (NIHSS) at 24-48 hours after thrombolysis treatment (and/or intra-arterial treatment if received): standard post thrombolysis stroke severity measurement.  
Complications (symptomatic intracranial haemorrhage / extracranial bleed / angioedema / other complication) within 48 hours of thrombolysis treatment (and/or intra-arterial treatment if received): standard post thrombolysis complications measurement.

The post admission data are all routinely collected clinical data. They will be transcribed from routine medical records onto a study specific hospital CRF. This will be performed by NHS research support staff or other clinical staff trained to deliver this research project.

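### The SAE exclusion for thrombolysis-related cerebral haemorrhage has no time limit, but the record it relies on stops at 48 hours, leaving a small safety-capture gap up to day 7

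*Protocol*

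**What the plan says.** All references are to the protocol.

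- **Reporting window** (section 17, Recording and reporting of adverse events): apart from death, "adverse events which are considered to be serious will only be reported up until seven days after study entry". Deaths are followed to 90 days.
- **Exclusion** (same subsection): the first item excluded from SAEs is "The expected adverse events listed above (these will be routinely recorded and monitored as part of study data collection".
- **What the exclusion covers** (section 17, Expected adverse events): the list includes "Thrombolysis related cerebral haemorrhage". It sets no time window and refers to no definition elsewhere.
- **The record relied on** (section 13, Day 2 thrombolysis outcome): "Complications (symptomatic intracranial haemorrhage / extracranial bleed / angioedema / other complication) within 48 hours of thrombolysis treatment".
- **Definition of symptomatic haemorrhage** (section 10.2): a rise in NIHSS of at least 4 "points within 36 hrs of thrombolysis associated with parenchymal haemorrhage on repeat brain imaging".
- **Drug action** (section 17): the protocol states that the drug's effect has ended by 24 hours.
- **Day 90 items** (section 13): cause of death (after discharge, if available), readmissions with reason, and stroke recurrence, asked of patients still in hospital at day 90 and of those readmitted. No item asks about haemorrhage as a complication.
- **Catch-up** (section 17): the 90-day form prompts staff to look for unreported events, but only those that meet the SAE criteria.
- **Onward reporting** (section 17): "Serious adverse events, regardless of causality or expectedness, will be reported to the Chief Investigator".

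**The concern.** The exclusion rests on a premise: these events need no SAE form because the study data already hold them. For haemorrhage that is true only up to 48 hours after treatment. The exclusion itself has no such limit, and SAE reporting runs to day 7, a period the protocol says it chose for additional reassurance over 24 hours.

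Within that gap, whether an event is reported depends on the site's judgement of relatedness and on whether the patient was thrombolysed. Section 14 provides no blinding measures, so sites may know the allocation when they judge. The event in question is the main recognised harm of the treatment that the pathway is meant to deliver more often. At stake is whether the sponsor and the Chief Investigator would learn of a late haemorrhage at all.

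**Working it through.** **1. Where each event is recorded.** Take a new, serious intracranial haemorrhage in a participant and trace it through sections 13 and 17.

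| Event | SAE form | Study data |
|---|---|---|
| Treated, within 48 h, judged thrombolysis related | Excluded | Day 2 complications item |
| Treated, after 48 h to day 7, fatal | Excluded if judged related | Death, date and cause |
| Treated, after 48 h to day 7, after discharge, readmitted | Excluded if judged related | Readmission and reason |
| Treated, after 48 h to day 7, judged unrelated | Reportable | SAE form |
| Untreated, up to day 7, still an inpatient | Reportable (not on the expected list) | SAE form |
| **Treated, after 48 h to day 7, non-fatal, still an inpatient, judged related** | **Excluded** | **No named item** |

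Only the last row has no home. The 90-day catch-up does not recover it, because an excluded event does not meet the SAE criteria. The recurrence question would reach it only if the site classed the bleed as a recurrent stroke and the patient was still in hospital at day 90.

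**2. The windows side by side.** Drug action: 24 hours (section 17). Definition of symptomatic haemorrhage: 36 hours from treatment (section 10.2). Complications item: 48 hours from treatment (section 13). SAE reporting: 7 days from the paramedic assessment (section 17). No sentence says which of them decides that a haemorrhage is thrombolysis related for the purpose of the exclusion.

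**3. Size.** Inputs from section 18 (Sample size): 856 control and 428 intervention analysable participants, with thrombolysis in 0.43 and 0.53. From section 17: 2% of treated patients deteriorate from cerebral haemorrhage.

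The arm sizes first. The two-proportion formula at 90% power, two-sided 5% and 2:1 allocation gives control n = [1.960 × √(0.4633 × 0.5367 × 3) + 1.282 × √(0.43 × 0.57 + 2 × 0.53 × 0.47)]² / 0.10² ≈ 783, so 783 × 1.5 = 1174.5 in total. The design effect is 1 + (5 − 1) × 0.02 = 1.08, which gives 1268 analysable, and 1268 / 0.99 ≈ 1281 recruited. The protocol's 1284 and 1297 are reproduced to within about 1.2%.

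Expected haemorrhages:

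- Control: 856 × 0.43 = 368 treated; × 0.02 = 7.4 events, or 0.86% of the arm.
- Intervention: 428 × 0.53 = 227 treated; × 0.02 = 4.5 events, or 1.06% of the arm.
- Total: about 12 events; difference between arms 0.20 percentage points.

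The documents do not give the share occurring after 48 hours. Assumed shares:

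| Assumed share after 48 h | Control | Intervention | Total | Difference (points) |
|---|---|---|---|---|
| 5% | 0.4 | 0.2 | 0.6 | 0.01 |
| 10% | 0.7 | 0.5 | 1.2 | 0.02 |
| 25% | 1.8 | 1.1 | 3.0 | 0.05 |
| 50% | 3.7 | 2.3 | 6.0 | 0.10 |

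These are upper limits for the gap at each assumed share, because they count every late haemorrhage, including fatal, readmitted and unrelated cases that are captured by other routes.

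**The case against.** The strongest reply is that the gap closes if the protocol is read as a whole. Only thrombolysis-related haemorrhage is excluded. Section 10.2 uses 36 hours and section 17 says drug action is over by 24 hours, so a bleed on days 3 to 7 would usually not be called thrombolysis related and would be reported as an SAE. The 48-hour item even outlasts the 36-hour definition. This has force, and it probably shrinks the gap. It does not remove it: the expected-events list neither cites that definition nor sets a window, so two sites could follow the text and handle the same day-4 bleed differently.

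A second reply is that keeping events already collected as outcomes off SAE forms is a reasoned choice, and that the DMEC can see unblinded outcome data. That stands for haemorrhages up to 48 hours, and is why the whole exclusion need not be lifted. It does not help with an event that no form collects.

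Third, the sentence sending SAEs to the Chief Investigator whatever their expectedness can be read as applying to what remains after the exclusions. That reading is workable. The wording is loose, but it is not a firm contradiction.

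A reader might also infer that late haemorrhages are recorded nowhere, or that the safety comparison is tilted towards the arm with more thrombolysis. The documents do not support either. Fatal cases carry a cause and readmissions a reason. Complications after thrombolysis are a secondary outcome (section 6.2), and safety outcomes are analysed by allocated group (section 18), so haemorrhages to 48 hours remain available for comparison by arm. The protocol names no between-arm test of SAE counts.

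**Conclusion.** The point holds in a narrow form. The reason given for the exclusion fails between 48 hours after treatment and day 7. A non-fatal haemorrhage in a continuing inpatient that the site judges thrombolysis related then has neither an SAE form nor a named data item, while the same event judged unrelated, or in an untreated patient, is reportable.

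The number affected is small: at most about 0.6 to 6 events in the whole trial, if 5% to 50% of some 12 haemorrhages occur late. That range is an assumption; the 2% and the thrombolysis rates are the protocol's. The direction would favour the arm treated more often, but by no more than 0.10 percentage points over that range. Even removing all 12 events would shift the arms by only 0.20 points. It is a safety-capture gap worth closing, not a shown bias in the trial's conclusion.

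**What to change.** In section 17, Recording and reporting of adverse events, limit the exclusion for this event, for example:

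*Thrombolysis-related cerebral haemorrhage is excluded only where it is recorded on the Day 2 form, that is, within 48 hours of treatment. Any new intracranial haemorrhage from then until day 7 that meets the SAE definition is reported as an SAE, whether or not the patient was thrombolysed.*

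Reporting for untreated patients before 48 hours stays as it is. The word *new* matters because patients presenting with haemorrhagic stroke are also enrolled. The alternative is to keep the exclusion and extend the haemorrhage item on the case record form to day 7.

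Also:

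- Reconcile the windows in section 10.2, the Day 2 item in section 13, and the two subsections of section 17, and state which one governs the exclusion.
- Keep the sentence on reporting to the Chief Investigator, since it provides that route, and add that it applies to SAEs remaining after the exclusions.
- Leave haemorrhage on the expected list, so that the REC rule for related and unexpected SAEs is unchanged.

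The cost is a wording amendment and a few more SAE forms (about six at the top of the assumed range), or one extended field. The existing 90-day prompt would pick up missed cases once they meet the SAE criteria, so no new procedure is needed.

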## 18. Statistical analysis

Analysis is by 'treatment allocated'; that is, primary and secondary efficacy and safety outcomes analyses will all use the study group allocation of the attending paramedic; only paramedics completing the study specific training will be considered as members of the intervention group. Thus, data will be analysed pragmatically according to paramedic group allocation, irrespective of the care process actually experienced by individual participants.

The primary end point measure is the proportion of participants who received intravenous thrombolysis. The primary analysis will compare the proportion of participants who received thrombolysis in the two arms of the study using logistic regression. Models will include various covariates and factors, including (but not limited to) participant age and gender and admission time and date (used to define a covariate to reflect background trends).

Secondary outcomes, including stroke severity 24 hours after thrombolysis (measured by an NIHSS score), inpatient mortality and dependency (modified Rankin Scale), will be analysed by appropriate ordinal and binary regression models, with appropriate adjustment for potential covariates and factors.

To address the second objective (that is, the impact of the intervention on various time intervals related to the emergency call), we will use appropriate statistical models. For time intervals between events which always happen (for instance, emergency call to hospital admission), we will employ linear models (after appropriate transformation), again adjusting for statistically significant covariates and factors; if the distributions of residuals are markedly non-normal, further transformation or bootstrapping will be considered. Residual diagnostics will also be used to identify outliers; identified outliers will be excluded and the analysis recalculated. For events which may or may not happen (for instance, emergency call to thrombolysis), we will analyse outcomes via binary regression models and survival analysis, comparing intervention and control arms using the framework of accelerated life testing; both approaches will again accommodate statistically significant covariates and factors.

Other clinical objectives will be addressed by appropriate descriptive statistical measures.

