## **9. Randomisation**

PASTA is a cluster RCT in which the unit of randomisation is an ambulance station or, in the case of large ambulance stations, an identifiable paramedic team within a station. Clusters comprise the paramedics based within teams or at stations. Randomisation will be performed prior to the start of the trial in each region. Within each ambulance service, ambulance stations or paramedic teams (according to local service configuration) which feed into a study hospital will be randomised to delivering the PASTA pathway or to continue with standard stroke care. All paramedics will be given the option of not assisting with the study.

Stations or teams within each service will be stratified according to size (categorised as small, medium or large according to the personnel and resources available), and distance from the nearest study hospital admitting stroke patients (distance categorised as near or far, reflecting the local geography of each ambulance service). The use of these stratifying variables will ensure that PASTA care paramedics (intervention) and standard care paramedics (control) are approximately equally matched by operational characteristics. The actual randomisations will be performed, documented and reported by two statisticians at Swansea University Clinical Trials Unit.

Stations and teams randomised to continuing standard care will be informed that there is an ongoing study of pre-hospital assessment for stroke patients, but not be given any further information about the intervention. For paramedics who are part of a station or team randomised to deliver the PASTA pathway, study specific training and documentation will be provided. Paramedics who opt out of the study or who work within a station or team that was not selected to be involved in the study will continue to deliver standard care.

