## **Sample size**

Sample size considerations are based on postulated and standardised statistical effects of the intervention on binary outcomes. A change from 0.1 to 0.13 (for instance, in the proportion of cases with a good mRS score at day 90) is equivalent to an effect of 0.1, while a change from 0.43 to 0.53 (for instance, in the proportion of patients receiving thrombolysis) is equivalent to an effect of 0.2.

In the initial protocol for this trial, sample size considerations assumed equal patient numbers per arm, allowed for 3% attrition for a primary outcome collected at day 90, used conventional values of 80% power and 5% significance, and a relatively small change between arms from 0.1 to 0.13 in the proportion of cases with a good mRS score at day 90, equivalent to a standardised statistical effect of 0.1. These considerations led to an initial recruitment target of 3640 (1820 cases per arm).

However, in early 2017, informal review of internal phase data showed that some key assumptions were unlikely to be met in practice. Specifically, overall recruitment was lower than anticipated, while intervention paramedic training completion rates meant a persistent imbalance in patient numbers in the two arms, with typically 8-10 control cases for every 5 intervention cases.

Following discussions with stakeholders (including both trial oversight committees and funders), it was agreed to amend the primary outcome to the proportion of patients receiving intravenous thrombolysis; postulating a change from 0.43 to 0.53 in the proportion of patients receiving thrombolysis, equivalent to a standardised statistical effect of 0.2. Sample size considerations were therefore re-assessed, factoring in attrition of 1%, power of 90% (and 5% significance), and an average cluster (patients per paramedic) of 5 with an intra-cluster correlation coefficient of 0.02. In addition, an imbalance of 2 control cases per intervention cases was incorporated. This gave a revised recruitment target of 1297 study participants (865 control cases versus 432 intervention cases).

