## **3. Paramedics**

Following the start of this research project, the scope of paramedic interviews has been amended. The first study protocol detailed interviews with only intervention group paramedics who had completed the study training. However as a significant proportion of paramedics randomised to the intervention group did not undertake the training, the process evaluation has become an important opportunity to understand barriers and facilitators to the deployment of the intervention if it was found to be of value for patient care, and about pre-hospital research in general. Therefore interviews have been widened to include intervention group paramedics who have not completed study training after a reasonable amount of time despite repeated invitation and opportunity to do so.

For intervention group paramedics who have completed training, purposive sampling will aim to ensure representation of a range of times since PASTA pathway activation (less or more than 30 days; no activations since training); paramedic seniorities (years of practice; employment title); base station setting (urban; rural); and experience of different patient admission routes (via ED; direct to stroke unit). These data are collected as part of the study or from individual paramedics during registration for training.

For intervention paramedics who have not completed training, selection for interview will aim to represent only each ambulance service and base station setting (urban; rural), as further information about non trained paramedics is not captured during the study processes.

According to availability, focus groups or individual interviews (in person or by telephone) will be conducted. Paramedics taking part in both the internal pilot trial (up to 20) and main trial (up to 60) will be included. Individual paramedics may be invited for interview on more than one occasion. For intervention group paramedics who have completed training, interviews will focus on understanding views about delivery of the study intervention and the training process. For intervention group paramedics who have not completed training, interviews will focus (as appropriate) on why training has not been undertaken and views on why they may or may not undertake training if the intervention was part of standard clinical care.

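### The analysis labelled 'treatment allocated' counts only trained paramedics as intervention, a one-sided selection after randomisation, so randomisation does not fully protect the primary comparison

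*Protocol*

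**What the plan says.** Protocol section 9 states that "the unit of randomisation is an ambulance station or, in the case of large ambulance stations, an identifiable paramedic team within a station". Section 18 names the analysis 'treatment allocated' for efficacy and safety outcomes and says that "data will be analysed pragmatically according to paramedic group allocation, irrespective of the care process actually experienced by individual participants". Between those two statements it adds the membership rule: "only paramedics completing the study specific training will be considered as members of the intervention group".

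Section 15 shows what the rule requires. Intervention paramedics watch an online video and count as trained only when every test question is answered correctly; those who "do not wish to assist with the study, they will be able to opt out of training". Control paramedics receive no training or test and can opt out.

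The effect is documented. Section 21 (Paramedics) reports that "a significant proportion of paramedics randomised to the intervention group did not undertake the training". The sample-size text in section 18 attributes a persistent imbalance to training completion, "with typically 8-10 control cases for every 5 intervention cases", and builds a 2:1 ratio into the revised target. The sensitivity analyses named in section 18 are by treatment received and by unchanged diagnosis, plus unspecified others. None is by randomised station or team.

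**The concern.** Completing training happens after randomisation and depends on the paramedic's own choice and test result. Paramedics who complete it may differ from those who do not in ways that affect thrombolysis, such as how reliably they pre-notify. Section 10.1 itself says compliance with pre-notification is variable under standard care. The control arm keeps both kinds of paramedic, apart from opt-outs. Any difference that existed before training would be attributed to the pathway, or would mask its effect if it ran the other way.

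The stratified randomisation in section 9 balances all randomised stations and teams. It gives no such assurance for the subset of paramedics who trained. A reader told that the analysis is by allocation would credit the comparison with more protection than it has, and recruiting more patients would not remove the problem.

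**Working it through.** **Inputs (Protocol section 18).** Thrombolysis 0.43 v 0.53; two-sided 5%; 90% power; attrition 1%; 5 patients per paramedic; intra-cluster correlation (ICC) 0.02; 2:1 ratio; 856 control and 428 intervention analysable; observed imbalance 8-10:5.

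**1. The plan's own figure.** Design effect = 1 + (5 − 1) × 0.02 = 1.08. With the stated standardised effect of 0.2, control n = (1.96 + 1.2816)² × (1 + 1/0.5) / 0.2² = 788. Total = 788 × 1.5 × 1.08 = 1,277 analysable, and 1,277 / 0.99 = 1,290 recruited. The pooled two-proportion formula gives 1,268 and 1,281. The protocol states 1,284 and 1,297. Power at 856 v 428 is 90.4%. The arithmetic is sound for the comparison as defined, which is trained intervention paramedics against controls.

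**2. Share outside the comparison.** Assume the randomised arms would yield equal patient numbers and that training completion alone causes the imbalance. The share lost is 1 − 5/8 = 37.5% to 1 − 5/10 = 50%. The protocol does not state the randomisation split.

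**3. How large could selection bias be?** The ICC limits how much paramedics differ. Between-paramedic SD = √(0.02 × 0.43 × 0.57) = 0.070, or 7.0 points. Take paramedic effects as roughly normal and suppose, at the extreme, that exactly the best performers train. For a trained share t, the trained mean exceeds the overall mean by SD × φ(c)/t, where c is the cut-off leaving a share t above it.

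- t = 0.50: 7.0 × 0.3989/0.50 = 5.6 points
- t = 0.625: 7.0 × 0.3792/0.625 = 4.2 points

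These are ceilings. If training uptake correlates with performance at r, the bias is about r times the ceiling:

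| Bias | r needed at t = 0.50 | r needed at t = 0.625 |
|---|---|---|
| 1 point | 0.18 | 0.24 |
| 3 points | 0.54 | 0.71 |
| 5 points | 0.90 | not attainable |

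A modest r of 0.3 gives 1.3-1.7 points.

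**4. Effect on the false-positive rate.** SE = √(0.43 × 0.57 × (1/856 + 1/428) × 1.08) = 0.0305. With no true effect and bias b, the chance of a significant result is Φ(b/SE − 1.96) + Φ(−b/SE − 1.96).

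| Assumed bias | Chance of a significant result |
|---|---|
| 0 | 5% |
| 1 point | 6% |
| 2 points | 10% |
| 3 points | 17% |

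**5. Analysis by randomised station or team.** If untrained paramedics deliver the control rate, the 10-point effect dilutes to 10 × 0.625 = 6.25 points or 10 × 0.50 = 5.0 points. With 856 analysable per arm and design effect 1.08, power is about 70% or 52%. Restoring 90% power would need about 2,913 or 4,545 recruited.

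**The case against.** The strongest reply is that the design remains randomised: stations and teams were allocated with stratification, selection acts only on paramedics within those clusters, and control paramedics can also opt out. The rule is stated openly beside the label. Patients of trained paramedics stay in the intervention group whatever care they received. All of this stands. A reader might infer that the comparison is simply self-selected, or that it is a per-protocol analysis; the documents support neither. They support a modified allocation analysis with selection in one arm.

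A reader might also infer that patients are deleted after enrolment. Section 18 does not say so. Section 12 identifies patients through the identification numbers of paramedics involved in the study, so patients of untrained intervention paramedics probably never enrol. Their absence still leaves the arms selected differently.

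A 5-point bias, which would give a false-positive rate of about 37-38%, is another tempting figure. Under the protocol's ICC it lies at or beyond the extreme (step 3), although the ICC is itself a planning value.

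On adjustment, the covariate list in section 18 is expressly open, and section 15 collects paramedic characteristics in order to see whether the groups differ. Leaving the full model to the statistical analysis plan is normal. What remains is that the protocol ties no analysis to these data. Finally, section 15 says "the following will be obtained about individual randomised paramedics during the course of the study", while section 21 says that "further information about non trained paramedics is not captured during the study processes". This could be read as proof that untrained paramedics will go undescribed. Section 21 concerns the choice of interviewees, and section 15 allows collection from service records or a survey, so this is mostly a matter of wording.

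**Conclusion.** The label in section 18 is wrong as written. Membership of the intervention group depends on behaviour after randomisation, in one arm only, and the protocol's own account shows that the resulting loss is large. Randomisation therefore does not fully protect the primary comparison.

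The 37.5-50% rests on equal expected patient numbers in the two arms. The documents do not give the direction or size of the bias. A range of 1-3 points is an assumption compatible with the ICC of 0.02; its upper end already needs a fairly strong link between training uptake and performance. The result is a weakened and mislabelled comparison. The documents do not show that the trial's result would be invalid.

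**What to change.** **(a) Label and scope.** Replace 'treatment allocated' with a description such as 'modified allocation: trained intervention paramedics v participating control paramedics'. State how patients of untrained intervention paramedics are handled. Report training completion and opt-out by arm. Limit the primary conclusion to paramedics who complete training. This costs wording only.

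**(b) Adjustment.** Adjust for the paramedic characteristics collected under section 15 and for the randomisation stratifiers (station size and distance), in the primary model or in a named key sensitivity analysis. Align section 21 with section 15 so that these data cover all randomised paramedics. This needs modelling and completion of a collection already planned.

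**(c) Sensitivity analysis by randomised station or team, where data permit.** Use the same aggregate or de-identified source and the same inclusion rules in both arms, covering patients of untrained and opted-out paramedics. A log of unconsented patients in the intervention arm alone would not do, because it would mix consented and unconsented cases on one side. Report an estimate with a confidence interval, and note its dilution and its power of about 52-70% under the assumptions above. The primary conclusion should not depend on whether this analysis is significant. It needs an amendment and some additional de-identified data.
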